## Abstract

**Background:**

Cardiac rehabilitation after acute myocardial infarction permits recovery of the heart function and enables secondary prevention programs in which changes in lifestyle habits are crucial. Cardiac rehabilitation often takes place in hospitals without coordination with primary healthcare and is not focused on individual patient preferences and goals, which is the core of the motivational interview. The objective of this study was to evaluate the efficacy of a cardiac rehabilitation program with a motivational interview in patients discharged from hospital after acute myocardial infarction.

**Methods/design:**

A randomized, non-pharmacological clinical trial in six primary healthcare centers in Barcelona (Spain) will assess whether a tailored cardiac rehabilitation program consisting of four motivational interviews and visits with family physicians, primary healthcare nurses and a cardiologist, coordinated with the reference hospital, results in better cardiac rehabilitation than standard care. A minimum sample of 284 participants requiring cardiac rehabilitation after acute myocardial infarction will be randomized to a cardiac rehabilitation group with a motivational interview program or to standard primary healthcare. The main outcome will be physical function measured by the six-minute walk test, and the secondary outcome will be the effectiveness of secondary prevention: a composite outcome comprising control of blood pressure, cholesterol, diabetes mellitus, smoking and body weight. Results will be evaluated at 1,3 and 6 months.

**Discussion:**

This is the first clinical trial to study the impact of a new primary healthcare cardiac rehabilitation program with motivational interviews for patients discharged from hospital after myocardial infarction. Changes in lifestyles and habits after myocardial infarction are a core element of secondary prevention and require patient-centered care strategies such as motivational interviews. Therefore, this study could clarify the impact of this approach on health indicators, such as functional capacity.

**Trial registration:**

ClinicalTriasl.gov NCT05285969 registered on March 18, 2022.

## Background

Recovery of heart function after acute myocardial infarction (AMI) requires cardiac rehabilitation (CR) to ensure the best possible physical, mental, and social conditions to regain an active life [1, 2]. CR programs have been shown to reduce morbidity and mortality after AMI, and improve the quality of life and psychological wellbeing [3]. However, CR programs are not widely implemented in EU countries: after AMI, not all patients undergo CR, which varies from 3% in Spain to 90% in Lithuania [4].

CR programs include physical training, health education, psychological interventions and control and follow up of risk factors: smoking, hypertension, cholesterol levels, diabetes mellitus, obesity and sedentary lifestyles (physical activity) [4, 5]. CR programs are often divided into three phases, starting after stabilization of AMI: a) in-hospital, b) early outpatient phase, and c) maintenance [6, 7]. The European Society of Cardiology has focused on hospital-based CR programs, but they may also be outpatient led. Delivering hospital CR programs after AMI to all patients has two drawbacks: poor accessibility and delays in starting due to a lack of rooms and healthcare professionals. While the effectiveness of CR is greater if begun early, currently, most patients do not start CR programs one year after AMI, thus increasing the risk of a worse outcome [8]. A European study showed that only 45% of patients discharged from hospital after AMI with or without revascularization, were referred for CR and only 34% participated [9]. A possible solution to overcoming the barriers to CR programs would be to integrate CR into primary healthcare (PHC).

PHC centers facilitate health care in the community, and citizens have an assigned family physician and PHC nurse [10]. PHC health professionals coordinate with other healthcare professionals, such as cardiologists, and other healthcare settings, including hospitals [11, 12]. PHC services also include home-care programs for patients unable to attend the PHC center due to health problems or disability. PHC physicians and nurses are well positioned to care for patients requiring CR after AMI, because the main objectives are to control risk factors, improve patient self-management and decision-making in diet, exercise routines and weight control, etc. A review and a meta-analysis concluded there were no differences between CR at home or in hospitals with respect to mortality, reinfarction, revascularization, hospitalization, and exercise capacity [13, 14].

In CR, person-centered care is essential, including consideration of patients’ goals, values, previous routines, and environment [15, 16]. This approach requires communication skills, such as motivational interviews (MI). MI is a collaborative, goal-oriented style of communication with particular attention paid to the language of change [17]. In PHC, MI make it possible to establish common objectives that can be monitored agreed between patients and health professionals and which encourages motivation to change by exploring and solving patients’ ambivalence [18]. MI and CR are more effective in the early stages of the disease, for example, after AMI, when the patient is more likely to initiate lifestyle changes [19, 20]. Two systematic reviews showed that MI improved self-care in patients [21, 22] with heart failure. However, the effect of MI combined with a CR program after AMI is unclear. Therefore, in this protocol we plan to study the efficacy of CR using MI compared with the current PHC standard of care after hospital discharge for AMI.

## Methods/design

### Main objective

The main objective of the study is to evaluate the efficacy in functional capacity, lifestyle indicators and psychological wellbeing of a new CR program with MI carried out entirely in primary healthcare in patients discharged from hospital after AMI.

### Secondary objectives and hypothesis

(i) To compare improvements in functional capacity and changes in risk factors (secondary prevention). (ii) To evaluate the impact of the CR program according to adherence to therapy (drug treatment and physical activity program) and health service use and (iii) to evaluate the efficacy of the CR program based on psychological factors and quality of life after AMI.

The hypothesis of the study is that a PHC CR program with MI after AMI has a positive impact on functional and psychological wellbeing and quality of life compared to standard care.

### Trial design and study setting

This will be a randomized controlled trial with two arms: a PHC CR program including MI (Intervention group) versus PHC standard care (Control group). The study will be carried out in seven primary healthcare areas in Barcelona city with six assigned PHC centers, including family physicians, nurses and social workers. The six PHC provide healthcare to 187, 223 people [23] and coordinate actions with the Hospital Clinic of Barcelona, the public high-complexity reference hospital, with an assigned population of 540,000 [24]. Figure 1 shows a map of the area of influence of the PHCs and the location of the hospital. The trial was prospectively registered (before participant recruitment) on ClinicalTrials.gov (NCT05285969) on March 18, 2022.

**Fig. 1 Fig1:**
[figure not shown]
Partial map of Barcelona (1:30,000). Area of influence of the six PHC (blue), and the Hospital Clinic of Barcelona. The map was modified from the Cartographic and Geological Institute of Catalonia, which gave permission to reuse their data and content [36]

### Participants and eligibility criteria

Potential participants will be PHC patients admitted to the reference hospital due to acute coronary syndrome (diagnostic codes ICD-10: I20-I22) or post-unscheduled cardiac revascularization surgery (code ICD-10: 021x) and discharged to home in the area of the six PHCs. Inclusion criteria will be age > 18 years, indication for CR and voluntary participation. Exclusion criteria will be: (1) acute aortic disease, severe pulmonary hypertension, uncontrolled arrhythmia, decompensated heart failure or significant valvular or congenital heart disease, (2) heart valve and/or interventricular septum surgery, (3) diseases that prevent exercise, (4) osteoarticular diseases that severely limit exercise, (5) severe mental disorder (i.e. schizophrenia, bipolar disorder, major depression or autism, and severe forms of other disorders), (6) cognitive disability, (7) problems of verbal communication and, (8) inclusion in a hospital CR program.

### Intervention group

CR with MI will be structured in four sessions, with an optional fifth session, in the six months after discharge. The methodology of the MI sessions will follow the four-phase logical sequence of MI proposed by Rollnick and Millner 1) engage in collaborative relationships, 2) focus on a particular change, 3) evoke intrinsic motivations for change, and 4) plan an immediate step for change [25]. MI will be administered by nurses trained through a certified MI course, who will be offered additional support and counseling. Collaborators will meet at least once a month to standardize the intervention and follow up of issues regarding MI. Each MI session will have defined contents and objectives to ensure homogeneity. The objectives of CR and secondary prevention will be introduced from the first session, (i.e., to increase participation in activities of daily living and self-care and follow recommendations on safe physical activity). Table 1 describes the MI program and the content of each session. Interviewers will collaborate in the coordination of care, ensuring continuity and communication between PHC family physicians, nurses, and the cardiologist).

**Table 1 Tab1:** Description of the intervention, content and aims of MI sessions

Session	Schedule and location	Duration	Aims	Content Description
#1	72 h Home	45 min	Relationship between patient and interviewer. Promote involvement of participant in CR	Presentation. General information on the program. Examine experiences, knowledge, motivation, self-confidence and expectations of CR and prevention
#2	2nd week PHC	20–30 min	Strengthen commitment and link with professional. Increase self-efficacy. Strengthen motivation	Identify specific objectives of patient to adjust to the CR plan. Collaborative work on personalized CR. Support and active listening to participant concerns. Examine participant resources
#3	5th week PHC	20–30 min	Maintenance therapeutic link. Empower participants. Increase self-efficacy. Strengthen motivation	Collaborative work. Support and active listening to patient concerns and adaptation of RC. Examine resources, barriers, and facilitators of patients. Manage discrepancies and resolving ambivalence. Discourse of maintenance
#4	8th week PHC	20–30 min	Empower patients. Increase self-efficacy. Reinforce motivation to maintain CR plan and prevention	Collaborative work in adapting the CR plan of persons at home. Support and active listening to concerns for maintenance. Examine resources, barriers and facilitators of patients about the CR plan at home and in the community. Discrepancy management. Resolve ambivalence
#5 (Optional)	13th week PHC	2–30 min	Link maintenance. Empower participants. Increase self-efficacy	This session can be programmed according to the criterion of the interviewer and depending on the participant's status. Tasks: Collaborative work. Support and active listening to concerns. Adaptation to the CR plan. Examine resources, barriers and facilitators. Discrepancy management. Resolve ambivalence. Maintenance discourse management

### Standard care group

To standardize comparison with the MI group, all control group patients will receive a kit with information about the actions and procedures to follow (diet, physical activity, smoking cessation, and other recommendations on secondary prevention) and the home physical activity program. Home exercises will be adapted from cardiology guidelines from the United States, Canada and Europe [26]. The collection of data, analytical samples, and information (questionnaires, scales, and clinical information) will be the same as for the intervention group. A collaborating researcher will contact patients by telephone beforehand. Table 2 shows the SPIRIT chart [27], describing the schedule of enrollment, interventions, and assessments.

**Table 2 Tab2:** Schedule of procedures, template from the SPIRIT check list. **v**_**9**_* I an optional visit, according to participant status (see Table 1)

			**Week**													
			**0**	**1**			**2**	**4**	**5**		**8**	**12**	**13**		**23**	**24**
			**Visit**													
**Activity/Task**	**Group**	**Agent, health care professional**	**v-**_**1**_	**v**_**0**_	**v**_**1**_	**v**_**2**_	**v**_**3**_	**v**_**4**_	**v**_**5**_	**v**_**6**_	**v**_**7**_	**v**_**8**_	**v**_**9**_^*****^	**v**_**9**_	**v**_**10**_	**v**_**11**_
Eligibility screen	Both	Research collaborator	x													
Informed consent	Both	Research collaborator	x													
Allocation	Both	Research collaborator		x												
Data collection of participant status	Both	Research collaborator			x			x				x			x	
Motivational interview	Intervention	Research collaborator			x		x		x		x		x			
Follow up: family physician	Both	Family physician				x			x					x		x
Follow up: PHC nurse	Both	PHC nurse				x			x					x		x
Six-minute walk test	Both	Research collaborator						x							x	
Follow up: cardiologist	Both	Cardiologist of the PHC area								x						
Blood analysis	Both	Research collaborator										x			x	

### Strategies to improve adherence to the protocol

To maximize adherence, study collaborators will send reminders of data collection sessions and visits by phone. If patients do not attend, they will be contacted again to avoid losses. Sessions will take place at the initial product dispensing and each study visit thereafter. The only criteria for discontinuing the intervention will be hospitalization due to worsening status. All concomitant care and interventions for health reasons are permitted during the trial.

### Main outcome

#### Physical functional capacity

Improvement in aerobic capacity and resistance, measured by the six-minute walk test [28]

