**DUKE UNC-11** [43, 44]	Perceived functional social support	**Structure:** Self-administered, 11 items with Likert-type ratings ranging 1 to 5. Scores range from 11 to 55 points
		**Interpretation:** The higher the average score, the greater the perceived social support
**Montreal Cognitive Assessment** [45, 46]	Cognitive dysfunction screening	**Structure:** Professional administered consisting of 12 tasks of the following domains: visuospatial/executive (5 points), naming (3 points), attention (6 points), language (3 points), abstraction (2 points), delayed recall (5 points), orientation (6 points). Total scores range between 0 and 30
		**Interpretation:** A score < 26 might indicate cognitive impairment
**Patient Health Questionnaire. PHQ-9** [47]	Depressive symptoms	**Structure:** Self-administered, 9 items for screening, diagnosing, monitoring and measuring the severity of depression
		**Interpretation:** Scores and cut-points: 5, 10, 15, and 20 represent for mild, moderate, moderately severe, and severe depression respectively
**Hospital Anxiety and Depression Scale (HADS)** [48, 49]	Emotional distress (anxiety and depression)	**Structure:** Self-administered, 14 items (7 anxiety and 7 depression), with Likert-type ratings ranging 1 to 4. Total ranging from 0 to 21
		**Interpretation:** A total subscale score of > 8 points in each of the sub-scales might indicate depression or anxiety
**International Physical Activity Questionnaires (IPAQ)** [50, 51]	Frequency, duration and intensity of activity	**Structure**: Self-administered, 7 questions self-completed. Evaluates: intensity (low, moderate, or vigorous), frequency (days for week) and duration (time for day)
		**Interpretation:** Classifies the level of activity in three categories: low, moderate, and high. Permits individual results to be converted into METs
**Six-minute walk test** [28]	Aerobic capacity and endurance	**Structure:** Sub-maximal exercise test used to assess aerobic capacity and endurance. The distance covered over a time of 6 min is used as the outcome to compare changes in performance capacity
		**Interpretation:** Allows results to be converted from meters to METs. An increase in the distance walked indicates improvement in physical function
**The 13-item Patient Activation Measure (PAM-13)** [52, 53]	Patient activation (self-efficacy)	**Structure**: Self-administered. 13 items 4-point Likert scale. Total scores range from 0 to 100

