#### Participant timeline

Patients meeting the inclusion criteria will be asked to participate during hospital admission. Potential participants will be given written and verbal information about the study and, if they agree to participate, will be asked to complete the informed consent document. The study coordinator will assign patients to the study groups using a previously-generated blinded random sequence. Participants will be contacted to specify the date of the baseline data collection visit. Sociodemographic and baseline characteristics will be evaluated at the beginning of the study. Follow-up evaluations will be made at 1, 3 and 6 months. Baseline and follow-up evaluations will be made by researchers unaware of the group to which each patient is assigned. Figure 2 shows the study flowchart and timeline.

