### Statistical methods

Outcomes will be evaluated at 1, 3 and 6 months. Participant characteristics will be described using central tendency measures: mean or median and variability: standard deviation or interquartile range for continuous variables, and frequencies and percentages for categorical variables. The results of the physical functional capacity and the six-minute walk test will be transformed into units of metabolic equivalent of task (MET) using the equation and conversion table of the American College of Sports Medicine [33]. Between-group differences will be studied using the Student’s t-test for two samples. The magnitude of the effect will be calculated using Cohen's D. The effect of the intervention or standard care will be calculated using the Student’s t-test or Mcnemar’s test for paired samples. A mixed linear regression model will be used to evaluate trends in each arm, adjusting for variables of interest. For the inference analysis, co-variables that correlate (sociodemographic factors) will be used and adjusted analyzes made. In the comparison of multiple hypotheses, adjustment of the level of statistical significance (α = 0.05) will be used to avoid type I errors. All analyzes will made per protocol and intention-to-treat. The analysis will be made using R v3.5.2 [34].

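### The main outcome is an improvement in the six-minute walk, but the first walk test is at week 4, on treatment, so an improvement score would remove any effect already present by then

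*Protocol article*

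**What the plan says.** The Main outcome section gives one outcome: "Improvement in aerobic capacity and resistance, measured by the six-minute walk test". It names no reference time. Table 4 describes the walk distance as a measure that "is used as the outcome to compare changes in performance capacity".

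Table 2 has a separate row for the "Six-minute walk test", marked at v4 (week 4) and v10 (week 23) only. Allocation is at v0. Motivational interviews are marked at v1 (week 1), v3 (week 2), v5 (week 5), v7 (week 8) and, optionally, week 13. The row "Data collection of participant status" starts at v1, but the walk test is not marked there. Participant timeline states that "Sociodemographic and baseline characteristics will be evaluated at the beginning of the study", without naming a walk test.

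On early content, the Intervention group section says: "The objectives of CR and secondary prevention will be introduced from the first session".

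Statistical methods says "Outcomes will be evaluated at 1, 3 and 6 months". It plans a two-sample t-test between groups and paired tests within each arm, and adds that the walk-test results "will be transformed into units of metabolic equivalent of task (MET"). The Sample size section uses a 30 m difference, SD 80 m, two-sided alpha 0.05, beta 0.2 and 142 per arm.

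**The concern.** An improvement needs a starting value, and so does a paired test. The schedule offers none from before treatment. By week 4 the intervention arm has had two of its four planned interviews, and the rehabilitation objectives have been on the table since the first. A change from week 4 therefore measures only what the intervention adds between weeks 4 and 23. If patients benefit early, as the Background section expects when it says that both components work better soon after the infarction, that benefit is subtracted from the main result. The error favours a false negative on the trial's only main outcome.

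The stated assessment times do not match the schedule either. Table 2 has no walk test at 3 months, and blood is drawn only at weeks 12 and 23, so the LDL and HbA1c parts of the secondary composite have no 1-month value.

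**Working it through.** **Schedule.** Counting the Table 2 columns against the week row:

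| Item | Visits (week) |
|---|---|
| Allocation | v0 (1) |
| Interviews | v1 (1), v3 (2), v5 (5), v7 (8), v9* (13, optional) |
| Status data | v1 (1), v4 (4), v8 (12), v10 (23) |
| Walk test | v4 (4), v10 (23) |
| Blood | v8 (12), v10 (23) |

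Two interviews precede the first walk test, and no walk test precedes allocation.

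**What each analysis estimates.** Let Δ4 and Δ23 be the true between-arm differences at weeks 4 and 23, and ρ the correlation between the two distances, with equal SDs.

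- Week-23 distance: Δ23.
- Change score: Δ23 − Δ4.
- Week-23 distance adjusted for week 4: Δ23 − ρΔ4.

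**The plan's own figure.** n per arm = 2(1.960 + 0.842)² × 80² / 30² = 111.6, so 112 per arm or 224 in total (113 and 226 with the t-distribution). The stated 284 is not reproduced. It would follow from SD 90 m (141.3, so 142 per arm) or from about 20% dropout (113/0.80 = 141.3), neither of which is stated. That is a separate matter. Below, 142 per arm is taken as the number analysed.

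**Power of the change score.** Inputs from the Sample size section: Δ23 = 30 m, SD 80 m, 142 per arm, two-sided 0.05. Assumed, because the article gives neither: Δ4 of 5, 10 or 15 m, and ρ of 0.6 or 0.7.

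SD of change = 80 × √(2(1 − ρ)), which is 71.6 m at ρ = 0.6 and 62.0 m at ρ = 0.7. Power is for a two-sample t-test. As a hand check at ρ = 0.6 and Δ4 = 10: standard error = 71.6 × √(2/142) = 8.49, 20/8.49 − 1.96 = 0.395, power about 65%.

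| Δ4 (m) | Change score targets (m) | Power, ρ = 0.6 | Power, ρ = 0.7 |
|---|---|---|---|
| 5 | 25 | 84% | 92% |
| 10 | 20 | 65% | 77% |
| 15 | 15 | 42% | 53% |

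Comparing week-23 distance directly keeps the full 30 m and gives 88%.

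**Where the change score starts to lose power.** It falls below the direct comparison when (30 − Δ4)/SD of change < 30/80, that is, when Δ4 > 30 × (1 − √(2(1 − ρ))). This is 3.2 m at ρ = 0.6 and 6.8 m at ρ = 0.7.

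**Adjusting for week 4.** For Δ4 of 5, 10 and 15 m, the target is 27, 24 and 21 m at ρ = 0.6, and 26.5, 23 and 19.5 m at ρ = 0.7. The attenuation is milder than with the change score, but it does not vanish.

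**The case against.** The strongest reply is that the article never states that the between-arm test is on change. The Abstract gives the main outcome simply as physical function measured by the walk test, the sample size does not call its 80 m the SD of a change, and a two-sample t-test on 6-month distance fits both. Randomisation makes that comparison unbiased. This stands: a reader might infer that the plan has fixed a biased primary contrast, and the documents do not support that. They do define the outcome as an improvement and publish a schedule that has no valid starting value for one. An analysis plan can choose the contrast, but it cannot supply a pre-treatment test that was not scheduled.

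A second reply is that the early effect is unknown and may be small: the first interview is largely introductory and the second sets objectives. This also stands. With no effect at week 4 there is no bias. Nor does power always fall: at correlation 0.7 with 5 m present early, the change score has 92% against 88%. The general statement is about attenuation of the estimate, not loss of power.

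Three further inferences are tempting and should not be drawn:

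- That two walk-test times leave the type I error uncontrolled. Statistical methods promises an adjustment for multiple hypotheses, although it names no method.
- That the primary scale is open between metres and METs. Table 4 names distance as the outcome, and the MET conversion is not declared the primary test.
- That the secondary composite needs a baseline blood draw. It is defined by attained thresholds. Only its 1-month assessment conflicts with Table 2.

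**Conclusion.** The point holds as a mismatch between the outcome definition and the schedule. Taken literally, the main outcome can only be week 23 minus week 4, and that score understates the week-23 effect by whatever effect exists at week 4. The article leaves open whether this or 6-month distance is compared.

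The direction of the bias is certain if there is an early benefit. Its size cannot be derived from the document. The figures of 25, 20 or 15 m, and the power that goes with them, rest on the assumed early effects and correlations, on equal SDs at the two visits, and on all 142 per arm being analysed. The within-arm paired walk-test comparison has the same on-treatment reference. Separately, the stated assessment times contradict Table 2 for the 3-month walk test and the 1-month blood results.

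**What to change.** - Define the main outcome as six-minute walk distance in metres at week 23, compared between arms as randomised.
- Treat the week-4 test as an early outcome. Do not subtract it or use it as a covariate in the primary analysis.
- If covariate adjustment is wanted, use only variables fixed or measured before allocation, for example age, sex and ejection fraction at discharge, after confirming that the echocardiogram precedes allocation. Do not use weight as collected at v1, which follows allocation.
- Keep METs as a secondary presentation.
- Describe the paired week-4 to week-23 comparison as on-treatment change within an arm, not as the effect of the intervention.
- Replace the general 1, 3 and 6 months with the visits at which each outcome is actually measured.

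The cost is wording in the outcome and statistical sections, with no added visit or test. The downside is that the main outcome becomes attained distance rather than improvement, and the precision that a true baseline walk would have given is not available. The choice should be recorded before anyone sees outcome data by arm, since a contrast chosen later would look data-driven.
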